### Recruitment and randomization

Recruitment of patients undergoing radical open colon cancer surgery started on January 7, 2019 in three Czech hospitals (2 university and 1 regional). Patients fulfilling inclusion criteria are enrolled by the study anesthesiologist at the pre-anesthetic clinic and randomized into three arms according to the method of PA: 1. Continuous thoracic epidural analgesia, 2. Piritramide analgesia, and 3. Morphine analgesia. Randomization is performed using a computer-generated list with sequentially numbered containers (by a person not involved in the statistical analysis of the data). Demographic data, co-morbidities, cognitive function and physical status evaluations, chronic medication, preoperative oncologic therapy, laboratory test results, ASA status, and premedication are recorded into the study charts before surgery.

Blinding of the patients and operators is not possible due to clearly different types of intervention. The person performing data analysis will be blinded.

### Perioperative period

Patients are administered 400 ml/50 g carbohydrate pre-surgery drink, premedicated and anesthetized according to the standardized protocol which defines: perioperative medication, fluid therapy, hemodynamic goals and management, diuresis, core temperature, transfusion threshold, and postoperative nausea, and vomiting prevention. The protocol also defines analgesia corresponding with randomization (including a detailed standard of care for thoracic epidural analgesia). All the data are recorded including the length of anesthesia and surgery, and a brief description of the type of surgery and observed radicality.

Postoperative care is standardized including postoperative analgesia corresponding with randomization, hemodynamic optimization, fluid therapy and transfusions, glycemic control, and postoperative nausea and vomiting management.

A detailed description of perioperative and postoperative management in all three arms of the study is displayed in Fig. 2. The patients with insufficient pain relief on the protocol medication will be provided rescue multimodal analgesia with a strong opioid and will be excluded from the final analysis of the CTCs.

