## Background

Colorectal cancer (CRC) is the second most common cause of cancer-related deaths in Europe. Despite the progress in its early detection and adjuvant treatment, metastases are the leading cause of death in this group of patients. Although the development of postoperative metastases is a multifactorial process, it has been suggested that the mode of perioperative analgesia (PA) may play an important role in cancer recurrence (CR) [1, 2]. It has been proposed that avoiding opioids (particularly morphine) and employing regional analgesia techniques may have favorable effects on CR [1]. Such effects, if present, are probably attributable to less suppression of antitumor immune defenses due to:Better analgesia leading to a less pronounced perioperative stress reaction [1] which preserves anticancer immunity (particularly natural killer cells’ cytotoxicity). Such effects of epidural analgesia have been observed in open colectomy [3] and other major abdominal surgeries [4].Reduced exposition to volatile and intravenous anesthetics [1].Reduced exposition to opioids, especially morphine which exhibits negative effects on anticancer immunity and increases cancer cell proliferation, tumor progression [5, 6], and CR [2, 5, 7–10]. However, data on angiogenesis [8, 11–14] and cancer cell invasion [15, 16] are conflicting and some studies even show favorable immunomodulation [8].Positive effects of local anesthetics (cytotoxic and anti-proliferative). Indeed, promising results of in vitro [17] and animal studies showed that regional anesthesia decreases the risk of metastasis [5, 18, 19].

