### Primary outcome

The difference between the number of CTCs prior to surgery and 2—4 weeks after the surgery.

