### Sample size selection

Power analysis and sample size calculation stem from our prospective pilot data in 57 patients (17 patients with morphine, 19 patients with epidural, and 21 patients with piritramide analgesia). In this pilot study, we found a significant reduction in the number of CEA-mRNA positive CTCs (CEA = carcinoembryonic antigen) in systemic blood in 35% of piritramide- versus morphine-receiving patients. To confirm this effect, we expect a 35% decrease in CTCs in systemic blood in this ongoing study. We aim to demonstrate the effect in the epidural/piritramide analgesia groups at the level of 20%. Based on the power of 0.8 and the first type error of 0.05, we calculated the minimum number of subjects in the group to be 37. In order to compensate for a potential dropout of 10%, we decided to enroll minimum 40 patients per group, i.e. minimum 120 patients in total.

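### Patients who need rescue analgesia are dropped from the primary CTC analysis after randomisation, so the comparison is open to bias whose direction and size cannot be fixed from the document

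*Protocol article*

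**What the plan says.** The rule is in the protocol article, Perioperative period. It concerns "The patients with insufficient pain relief on the protocol medication", who "will be provided rescue multimodal analgesia with a strong opioid and will be excluded from the final analysis of the CTCs".

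Four other places bear on it:

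- **Primary outcome:** "The difference between the number of CTCs prior to surgery and 2—4 weeks after the surgery". The exclusion therefore applies to the primary comparison.
- **Recruitment and randomization:** patients "are enrolled by the study anesthesiologist at the pre-anesthetic clinic and randomized into three arms according to the method of PA". Allocation comes before surgery and before any rescue decision. The same section states that "Blinding of the patients and operators is not possible due to clearly different types of intervention"; only the person analysing the data is blinded.
- **Sample size selection:** 37 per group are needed, and "In order to compensate for a potential dropout of 10" per cent at least 40 per group are enrolled. Rescue exclusions are not mentioned.
- **Methods of data stewardship and analysis:** several candidate tests for CTC change are listed. No analysis of all randomised patients is named, and none that restores the rescued patients.

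**The concern.** Insufficient pain relief is a result of the randomised technique. Pain intensity is itself a secondary outcome. Removing patients because of it leaves, in each arm, those for whom that arm's technique worked, and randomisation does not make those subgroups comparable.

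Two conditions together produce bias: the need for rescue must be related to CTC change, and the rate or the causes of rescue must differ by arm. The Background makes both plausible. It proposes that regional techniques act partly through "Better analgesia leading to a less pronounced perioperative stress reaction [1] which preserves anticancer immunity". On that reasoning, pain control differs by technique and bears on the biology that the primary outcome is meant to reflect.

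If both conditions hold, the trial can report a difference between techniques that comes from who was removed, or can hide a real one.

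**Working it through.** **1. The plan's own figure.** The article gives 37 per group for power 0.8 and type I error 0.05, but no SD, baseline rate or sidedness, so 37 cannot be reproduced uniquely. Taken as a two-sided comparison of two means (normal approximation), it implies a standardised difference of (1.960 + 0.842) × √(2/37) = 0.651; a t-test gives about 0.66. These are back-solved values, not figures from the article.

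**2. Room for exclusions.** 37/(1 − 0.10) = 41.1, so 42 per group would cover a 10% loss. The plan enrols a minimum of 40, and 40 − 37 = 3 losses, or 7.5%. A 10% dropout alone leaves 40 × 0.90 = 36. If rescue exclusions come on top (rates assumed, power at 0.651):

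| Rescue rate | Evaluable per group | Power |
|---|---|---|
| 0% | 36 | 0.79 |
| 10% | 36 × 0.90 = 32.4 | 0.75 |
| 20% | 36 × 0.80 = 28.8 | 0.70 |
| 30% | 36 × 0.70 = 25.2 | 0.64 |

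**3. Bias when there is no true effect.** The article gives no rescue rate and no pain–CTC correlation, so both are assumed. Let a standard normal factor U drive the need for rescue and have correlation ρ with CTC change. Exclude the fraction q with the highest U. The mean of U among those kept is −m(q), where m(q) = φ(z)/(1 − q) and z is the (1 − q) quantile.

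- m(0.05) = 0.109
- m(0.20) = 0.350
- m(0.30) = 0.497

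The bias between two arms is ρ × [m(q₂) − m(q₁)], in SD of the outcome. Type I error comes from simulation (40 per arm, two-sided t-test at 0.05).

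| Rescue by arm | ρ | Bias (SD) | Type I error |
|---|---|---|---|
| 5% vs 20% | 0.3 | 0.3 × 0.241 = 0.07 | about 6% |
| 5% vs 20% | 0.5 | 0.5 × 0.241 = 0.12 | about 8% |
| 5% vs 30% | 0.3 | 0.3 × 0.388 = 0.12 | 7–8% |
| 5% vs 30% | 0.5 | 0.5 × 0.388 = 0.19 (simulated 0.20) | about 12% |

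**4. When the bias vanishes, and when it does not.** With ρ = 0 the bias is zero whatever the rates. With equal rates and the same cause of rescue it is also zero. With equal rates but different causes (pain-related in one arm, an unrelated technical failure in the other), 10–20% rescue gives 0.06–0.18 SD for ρ of 0.3–0.5. Unequal rates are therefore neither sufficient nor necessary.

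**The case against.** The best defence of the rule is that rescue brings in a strong opioid, which in the epidural arm is the exposure being compared. Keeping those patients dilutes the contrast. This stands as a cost. Take a t-test, a 0.66 SD effect, 40 per arm, and 20% rescued in one arm. Excluding them gives power of 78%. Keeping them gives 75% if rescue halves their contrast, since 0.66 × (1 − 0.20 × 0.5) = 0.594, or 65% if rescue removes it (0.66 × 0.80 = 0.528). At 30% rescued the figures are 75% against 70% or 53%. All these inputs are assumptions, but power does not favour the change. The defence does not rescue the rule as the primary analysis: the stated aim is to identify optimal analgesia techniques, and failure of a technique is part of how it performs.

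Second, the link between pain and the outcome is conjectural. Pain is scored over 72 hours, CTCs at 2–4 weeks, and the Background hedges its mechanism. This stands against any claim about size, though not against the structural defect.

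A reader might also infer the following, which the document does not support:

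- **Bias follows whenever rescue rates differ.** A relation with CTC change is also needed.
- **The technique that fails most often is favoured.** This holds only in the model above, where removed patients have the worse CTC results. The article does not show that this is so, or which arm will need more rescue.
- **Unblinded staff make the rescue decision.** The article says that patients and operators are unblinded. It does not say who judges pain relief, and the management figure is not shown.
- **Rescue exclusions lie outside the 10% allowance.** Dropout is not defined, so they may or may not be included.
- **The evaluable number will fall below 37.** That depends on an unstated rescue rate, and 40 is a minimum.

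**Conclusion.** The concern holds. The article states the exclusion outright, so it is a rule and not a detail left to a fuller document. Followed as written, the primary CTC comparison is not between randomised groups and is biased if the need for rescue is related to CTC change and its rate or causes differ by arm. Neither the direction nor the size of that bias can be fixed from the document.

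The 0.07–0.20 SD and the 6–12% type I error are illustrations that rest on assumed rescue rates (5% vs 20–30%) and correlations (0.3–0.5). For scale, 0.20 SD is about 31% of the 0.651 SD that 37 per group would detect (0.20/0.651), but that is the most extreme of the scenarios tabulated. The shortfall below 37 per group is possible, not established.

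**What to change.** In Perioperative period, delete the clause that removes rescued patients from the final CTC analysis. State, here and in the analysis section, that:

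- the primary CTC analysis includes every randomised patient with samples, in the assigned arm, whether or not rescue was given;
- the analysis without rescued patients is a labelled sensitivity analysis;
- rescue counts are reported by arm.

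In Sample size selection, say whether rescue exclusions are part of the dropout allowance, since they would still reduce the sensitivity analysis.

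The cost is a few sentences. Three blood samples are already planned from each patient (Sample collection, transport, and molecular biology analysis), so no extra patients or samples are needed, and rescue treatment itself is untouched. The price is possible dilution of the contrast between techniques and somewhat lower power than with exclusion. That is accepted in return for a comparison protected by randomisation.

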**Fig. 2 Fig2:**
[figure not shown]
Detailed protocol of perioperative management

All the data are recorded to the patient´s electronic CRF, using academic cloud operated software ClinData (https://clindata.imtm.cz), including pain intensity (using the Numerical Rating Scale) and sedation (using the Richmond Agitation-Sedation Scale), adverse effects and complications directly associated with PA, postoperative nausea and vomiting, core temperature, duration of postoperative ileus, laboratory tests, and cognitive function evaluation.

### Data monitoring

Data and the results of the trial will be audited and evaluated by the grant provider with its independent assessors. A trial progress report is submitted annually to the grant provider. The trial may be interrupted or terminated by the Ethical Committees of the institutions involved in the study or by the grant provider if there is a severe violation in the conduct of the trial or obvious harm to the participants. Adverse events are monitored at each site and immediately reported to the Ethical Committee and the grant provider. Potential protocol amendments are processed according to the Helsinki declaration.

### Sample collection, transport, and molecular biology analysis

In total, three samples of 9 ml of peripheral blood are collected into stabilization tubes (Streck cell-free DNA BC) from each patient: prior to anesthesia induction, on day 2, and on day 14–30. The amount of blood collected corresponds with other studies utilizing CytoTrack technology [40, 41]. We have chosen the sampling from the peripheral vein because it would not be possible to establish central venous access weeks after the surgical procedure. Stabilized samples are transported by express post/parcel service from participating hospitals to the Institute of Molecular and Translational Medicine (IMTM) on daily basis.

After delivery, blood samples will be immediately processed. After centrifugation at 2500 g for 15 min, the buffy coats will be further purified and stabilized using FACS lysing solution (BD Biosciences, San Jose, CA, USA) and subsequently stained with Cytotrack Reagent Kit (2C A/S, Copenhagen, Denmark) containing DAPI and anti-EpCAM, anti-panCK and anti-CD45 fluorescent- labeled antibodies. The immunostained cells will be applied on glass cytodiscs and scanned using an automatic fluorescent microscope CytoTrack CT11 (2C A/S, Copenhagen, Denmark). The CTCs number will be based on cell morphology, nuclei presence, and antibody expression (CK20 + , EpCAM + , CD45-) according to general recommendations.

The number of single CTCs and CTCs clusters is analyzed within each sample. If feasible, also the expression and activity of various receptor subtypes in cancer tissue would be analyzed.

### Methods of data stewardship and analysis

A transparent database for safe and efficient clinical data collection and stewardship was established within the ClinData software developed and deployed by the IMTM. The ClinData is open to all clinical centers for online management of the trial and recording of clinical and laboratory data. The data are converted into numeric codes for anonymization and follow-up processing.

Statistical analysis will be performed by an experienced biostatistician working full-time at the IMTM. Analysis of covariance (ANCOVA), repeated ANOVA tests or a non-parametric approach (Wilcoxon test, Kruskal–Wallis test) will be used to assess differences between respective groups with regard to changes in the number of CTCs before and after surgery. Cut-off values for the detection of CTCs and receptor expressions will be established using bootstrap methods. As feasible, the Kaplan Meier method will be used to analyze overall and/or disease-free survival and the log-rank test will be used to assess differences between respective groups. Alternatively, Cox regression analysis will be employed.

### Follow-up

A. Short-term (2–4 weeks after surgery): In all centers, sampling of peripheral venous blood is performed for the purpose of molecular analyses. Other standard laboratory tests including concentrations of tumor markers are performed. The length of hospital stay, postoperative complications as well as histology of the tumor are recorded.

B. Long-term (up to 5 years): We intend to follow the patients up beyond the duration of this project with regard to metastasis development according to current standards. Disease-free survival and cancer-specific and/or overall survival will be recorded.

### Dissemination

Study results will be disseminated through posters/lectures at regional and international conferences. We intend to publish a scientific manuscript in a peer-reviewed journal.

## Data Availability

The datasets generated and/or analyzed during the current study will be available at the: https://figshare.com following the completion of the trial. Model consent form for the participants is provided in Appendix 1.

## Abbreviations

ANOVA: Analysis of Variance
ASA: American Society of Anesthesiologists
CD45: Cluster of differentiation 45
CEA: Carcinoembryonic antigen
CK20: Cytokeratin 20
CR: Cancer Recurrence
CRC: Colorectal Cancer
CTCs: Circulating Tumor Cells
DAPI: 4’,6-Diamidino-2-phenylindole
DTCs: Disseminated Tumor Cells
EpCAM: Epithelial Cellular Adhesion Molecule
IMTM: Institute of Molecular and Translational Medicine
PA: Perioperative Analgesia
SPIRIT: Standard Protocol Items: Recommendations for Interventional Trials
